## **Outcomes: Primary and secondary**

The primary outcomes of this study are the proportion of participants who have altered VA behaviours defined by the objective eye-tracking data (e.g., saccades and fixations). Secondary outcomes are related to the change in team performance and workload due to impact of a team lead with a standardised checklist.

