## **Outcomes: Assessment**

### *Visual attention (situation awareness)*

Will be conducted with the wearable eye tracker (Pupil Labs, Core Eye Tracker, Berlin, Germany. 160×51mm, high speed 120Hz and 200Hz, <https://pupil-labs.com/products/core>). This wearable eye-tracker is modular, easy to clean (disinfect), durable, lightweight, and ergonomically designed for safe use and deployment in any settings. It is fully mobile as it connects to a smartphone for data capture ensuring the wearer is free to move and their normal movement activity are not restricted. Data is wirelessly transferred to Pupil Labs proprietary software and stored locally. Data will then be stored on a secure server where further analysis of those data will be made using a custom-made MATLAB® (MathWorks Inc, Massachusetts, USA) algorithm

From all the simulation eye-tracking videos, the following will be analysed:

- i. Descriptors pertaining to AOI on: the baby, monitors (e.g., examining pulse oximeter), pressures on the T-piece resuscitation device (*neopuff*), mask technique, oxygen administration, endotracheal intubation (if applicable), performance of procedures like umbilical vein catheterisation, team members, and timer on the resuscitaire.
- ii. Time spent on each AOI (indicating VA distribution).
- iii. Three eye movements including fixations, saccades and smooth pursuits.

Analysis of eye tracking videos will be performed by the research team. However, one of the limitations of eye tracking is that it does not capture the situations of “Inattentional blindness”. Meaning the operator may be looking at some aspect without putting their mind to it. This will be studied by using having an additional camera in the room to gather more (situational) detail in context.

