### *Visual attention*

During each simulation participant visual attention will be objectively assessed with a wearable eye-tracker, as previously described.

*Table S2: Visual attention outcomes*

|                                        | All scenarios
(Between participant comparison) |        |        | Within team post comparison
(Same person comparison) |        |        |
|----------------------------------------|---------------------------------------------------|--------|--------|---------------------------------------------------------|--------|--------|
|                                        | Nurse                                             | Tier-1 | Tier-2 | Nurse                                                   | Tier-1 | Tier-2 |
| AOI (description)                      |                                                   |        |        |                                                         |        |        |
| Time on AOI (seconds)                  |                                                   |        |        |                                                         |        |        |
| Time-to-first fixation (seconds)       |                                                   |        |        |                                                         |        |        |
| Saccades (mean and variability)        |                                                   |        |        |                                                         |        |        |
| Fixations (mean and variability)       |                                                   |        |        |                                                         |        |        |
| Smooth pursuits (mean and variability) |                                                   |        |        |                                                         |        |        |

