## Sample size

In a previous study using eye tracking glasses examining VA during neonatal resuscitation, in which the operator acted both as an airway manager and team leader. In this study operator spent 35% (SD 8) of time focused on the infant. With the presence of dedicated resuscitation leader, to improve the VA on the infant to 55% with 80% power and alpha error of 0.05, we will need to conduct 6 scenarios with 3 samples in each group (equalling 18 participants).

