## Statistics

This is an exploratory study consisting of XXX groups. To the authors knowledge, there has yet to be a comprehensive analysis of VA with eye-tracking in neonatal simulations examining impact of a team lead with a checklist. However, there has been a pilot study using eye-tracking in neonatal resuscitation which used a dataset of 6 participant video-based eye-tracking recordings of 5mins duration. Therefore, our anticipated dataset size of 24 participants, will provide greater insight to examine VA behaviour differences and detect impact of a team lead with a standardised checklist. Data will be analysed in SPSS (v23, IBM) and R studio (R. RStudio, Boston, MA, USA). To conform to the exploratory nature of the work, descriptive statistics such as means, and ranges will be used here based on the number of participants stratified across 4 teams. Independent t-tests will further explore any observable differences. Those data will be complimented with simple plots. Anonymised data will be made available on reasonable request.

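### The t-tests are chosen after the data are seen, and the one contrast the study was sized on is never named as primary, so nominal p-values cannot be read at 5%

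*Protocol*

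**What the plan says.** The Statistics section calls the study exploratory, puts means and ranges first, and then adds: "Independent t-tests will further explore any observable differences". It names no variable, contrast, number of tests or threshold. The same section says the dataset "will provide greater insight to examine VA behaviour differences and detect impact of a team lead with a standardised checklist".

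Under Outcomes: Primary and secondary, the primary outcomes are plural. They are proportions of participants with "altered VA behaviours defined by the objective eye-tracking data (e.g., saccades and fixations", followed by nothing that closes the list. The assessment section on visual attention lists nine areas of interest (AOIs), time on each, and "Three eye movements including fixations, saccades and smooth pursuits". Table S2 adds time to first fixation, and mean and variability for each eye movement. It sets these out for nurse, tier-1 and tier-2, in two comparison blocks.

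The Sample size section rests on one quantity. For the reference condition it gives "In this study operator spent 35% (SD 8) of time focused on the infant", and the aim is "to improve the VA on the infant to 55% with 80% power and alpha error of 0.05". That quantity does not reappear as the primary outcome or in the Statistics section.

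**The concern.** A rule that tests whatever looks different does not have the error rate of one test fixed in advance. The differences most likely to be selected are those that chance has made large. A reader who sees alpha 0.05 in Sample size and talk of detecting an impact in Statistics could take any p<0.05 in the gaze results as a leader effect at the 5% level.

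The contrast that justified the sample size would have no protected place. If it showed nothing while another gaze measure did, the protocol gives no basis for saying which result answers the primary aim. The stated primary outcome (a proportion of participants) and the sized quantity (a mean percent of time) are also different variables, so the text does not settle the matter by implication.

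**Working it through.** **1. The plan's own figure.** Inputs from Sample size: means 35% and 55%, SD 8, alpha 0.05 (taken as two-sided), power 80%.

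n per group = 2 × [SD × (1.960 + 0.842) / difference]² = 2 × [8 × 2.802 / 20]² = 2.51, rounded up to 3.

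The stated 3 per group is reproduced by this normal approximation. The calculation is for one variable and one comparison.

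**2. How many tests the rule could draw on.** The protocol gives no count, so three readings are shown.

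- *13 tests, operators only:* 9 AOI times + 1 time to first fixation + 3 eye movements. The Briefing section mentions the eye tracker only for airway operators.
- *24 tests, operators only:* 9 AOI times + 9 times to first fixation (one per AOI, an assumption) + 3 eye movements × 2 (mean and variability tested separately, an assumption).
- *72 tests:* 24 × 3 staff grades, using all three role columns of Table S2.

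**3. Independent tests, no effect.** Chance of at least one p<0.05 = 1 − 0.95^k.

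- k = 1: 5%
- k = 13: 49%
- k = 24: 71%
- k = 72: 98%

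**4. Allowing for correlation.** The measures come from the same few people, and each team is seen under both conditions (Study algorithm). Null studies were simulated with normal data, 3 versus 3, and an unpaired t-test on 4 degrees of freedom. ρ is the correlation between measures and r the correlation between a person's two runs; the staff grades are taken as independent. The document gives neither ρ nor r.

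| Tests | ρ=0, r=0 | ρ=0.3, r=0.3 | ρ=0.5, r=0.5 | ρ=0.8, r=0.5 |
|---|---|---|---|---|
| 13, operators only | 49% | 31% | 20% | 13% |
| 24, operators only | 71% | 48% | 30% | 18% |
| 72, three grades | 98% | 86% | 66% | 45% |
| Rejection rate of each single test | 5% | 3% | 2% | 2% |

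The last row shows that an unpaired test on repeated observations is conservative, and the other rows already include this.

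**5. Effect of selecting by eye.** These figures assume that every listed measure is tested. Testing only the differences that look large cannot exceed them. It stays close to them when the choice favours differences that are large relative to their spread, which a display of means and ranges encourages.

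**The case against.** The strongest reply is that the study is declared exploratory, that descriptive statistics come first, and that the t-tests are there only to explore further. No p<0.05 rule is attached to them: 0.05 appears only in Sample size. The remark about detecting an impact comes in a sentence comparing the dataset with an earlier pilot. A full list of tested variables and any multiplicity adjustment commonly belong in an SAP, which is not at hand. All of this stands, and the lack of an adjustment is not counted here as an error.

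A reader might also infer that the plan would produce a false-positive finding in roughly 66–98% of studies. The documents do not support that. The range needs the full 72-test grid, which counts time to first fixation once per AOI, mean and variability as separate tests, and all three grades as wearing the tracker. Intubation is an AOI only if applicable, and umbilical access is described as a need of the term scenario, so not every AOI need give a clean 3 versus 3 comparison. Smaller readings are at least as plausible and give much lower figures.

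The reply does not remove the selection rule itself. That rule is written into the protocol rather than left for later. Nor does it explain why a contrast sized at 80% power and alpha 0.05 is not the named primary.

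**Conclusion.** The point holds in a limited form. The protocol selects its t-tests from the data, leaves the primary outcome open, and does not name the sized contrast as primary or as tested. Nominal p-values from this rule cannot be read at 5%.

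The size depends on assumptions that the document does not settle: a p<0.05 threshold, the count of tests, normal data, ρ from 0 to 0.8 and r from 0 to 0.5. Across these, the chance of at least one nominally significant result with no effect runs from about 13% (13 measures, operators only) to 98% (72 independent tests). Even the lowest figure is more than twice 5%. The study remains usable as exploratory work; the defect lies in what its p-values could be taken to mean, and it should be corrected.

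**What to change.** Change Outcomes: Primary and secondary and Statistics together, so that they agree with Sample size:

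- Name the airway operator's percent of time on the infant, with versus without a dedicated leader, as the single primary variable and contrast. State that it is fixed before any recordings are summarised. Let it replace the open-ended proportion of participants, or state how the two relate.
- Analyse it within person or team (paired) where the same person is operator in both runs, and say what is done where that is not so.
- Report all other gaze, staff-grade and AOI results, and the NRPE and NASA-TLX secondary outcomes, as estimated differences with 95% confidence intervals labelled exploratory. State that no claim of a leader effect will rest on them.

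This takes a few sentences and no further participants or data. Confirmatory p-values for the other measures are given up. With three teams a paired test has 3 − 1 = 2 degrees of freedom, against 2 × 3 − 2 = 4 for the unpaired test, so the power statement should be recalculated for the analysis finally named.

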## Discussion

Here we provide a protocol for eye-tracking in neonatal resuscitation, with a focus on examining the impact of a team lead with a standardised checklist. At present there is no gold standard or proposed method for incorporating a team lead and/or checklist into neonatal resuscitation. This protocol will allow consideration of the combined and interactive impact of a team lead with a checklist for the field, considering the attentional demands using wearable eye-tracking video data to collect objective data to examine behaviour through visual attention.

This assessment paradigm distinguishes therefore itself from other work in the field. To the authors knowledge, no research has examined impact of a team lead with a checklist through use of a wearable eye-tracker, while also considering the scenarios of term and preterm in neonatal resuscitation. Furthermore, there hasn't been attempts explore team performance and workload. Therefore, the development and synthesis of this protocol will provide an important step in quantitatively assessing behaviour for appropriate clinical practice in neonatal resuscitation.

This protocol does carry some limitations. Firstly, there are several equivalent technologies that could be used for objective eye-tracking. However, given the lack of protocols in neonatal resuscitation, we feel the proposed manuscript provides a pragmatic starting point to work on and develop in future research.


Figure S1. SPIRIT Figure

|                             | STUDY PERIOD |            |                                 |                            |       |           |       |
|-----------------------------|--------------|------------|---------------------------------|----------------------------|-------|-----------|-------|
|                             | Enrolment    | Allocation | Post-allocation                 |                            |       | Close-out |       |
| TIMEPOINT**                 | $-t_1$       | 0          | $t_1$
(with
team
lead) | $t_2$ (no
team
lead) | $t_3$ | $t_4$     | $t_5$ |
| ENROLMENT:           |              |            |                                 |                            |       |           |       |
| Eligibility screen          | X            |            |                                 |                            |       |           |       |
| Informed consent            | X            |            |                                 |                            |       |           |       |
|                             |              |            |                                 |                            |       |           |       |
| Allocation                  |              | X          |                                 |                            |       |           |       |
| INTERVENTIONS:
NA |              |            |                                 |                            |       |           |       |
| ASSESSMENTS:         |              |            |                                 |                            |       |           |       |
| Participant details         |              | X          |                                 |                            |       |           |       |
| Visual attention            |              |            | X                               | X                          |       |           |       |
| Team performance            |              |            | X                               | X                          |       |           |       |
| Workload                    |              |            | X                               | X                          |       |           |       |
|                             |              |            |                                 |                            |       |           |       |

\*Recommended content can be displayed using various schematic formats. See SPIRIT 2013 Explanation and Elaboration for examples from protocols.

\*\*List specific timepoints in this row.
